#### 7.5. PRS Diagnostic Performance Study RV700 Imaging & AI Procedure

All subjects who are enrolled in the Diagnostic Performance Study will proceed to the RV700 Imaging & AI Procedure as outlined in Section 1.2.1. and 1.2.2. An operator, who has been provided with training by the Sponsor but who has no previous fundus imaging experience, will take images of the subject's left and right retina with an RV700 camera. The images will be immediately passed to IDx-DR for analysis. The operator will be masked to IDx-DR's diagnostic results but will be notified if the submitted images are insufficient for one or both eyes. If the images are not sufficient, the operator will receive an output of "Exam Quality Insufficient" and need to repeat the imaging process for that eye(s). If the operator receives three successive results

---

**Digital Diagnostics Confidential.** This document is intended for internal use only and may not be disclosed or reproduced in whole, or in part, for external distribution in any form without express written permission of DDx Legal. All hard copies should be checked against the current electronic revision prior to use and destroyed promptly thereafter. All hard copies are considered uncontrolled documents.

of “Exam Quality Insufficient” for either eye, the subject’s eyes will be dilated. The subject will first be asked to remove contact lenses if they are wearing contacts. Tropicamide 1% eye drops will be administered by qualified site staff under medical supervision. The subject will then be asked to wait at least 30 minutes or until the pupils are dilated to at least 5 mm. The operator will then attempt to image and submit images again. If after a further three attempts a diagnostic result is still not received, no further imaging attempts will be executed, PRS and the IDx-DR output for that/those eye(s) will be recorded as “Exam Quality Insufficient”. After the RV700 Imaging and AI Procedure is complete, subjects will advance to the PRS imaging protocol, the 4Widefield stereo & macular OCT Imaging Procedure performed by a FPRC certified ophthalmic photographer. The FPRC certified photographer will use a different, FDA-cleared camera system for widefield stereo color fundus photography as well as macular Spectral Optical Coherence Tomography (OCT) capability to perform dilated 4W four-field fundus photography and macular (OCT) imaging for each eye. Following the capture of the 4W and OCT images, the subject’s participation in the Diagnostic Performance main study will be complete.

After completion of the Diagnostic Performance Study, RV700, 4W and OCT images from each eye will be passed to retinal grading experts at a qualified reading center, who will independently determine the prognostic reference standard (PRS) for each eye from the 4W & OCT images, and ICDR grading from the RV700 images, and will be masked to each other and the IDx-DR diagnostic output. If the image is insufficient in any way, the ophthalmologist can record a determination of “ungradable”.

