| 1. To determine IDx-DR (using RV700) diagnosability, the percentage of eyes for which a diagnostic result can be provided.
2. To determine IDx-DR (using RV700) diagnosability, the percentage of subjects for which a diagnostic result can be provided.
3. To determine the positive and negative predictive values.
4. To investigate the effect of cases where no diagnostic result can be provided on sensitivity and specificity using a “worst case scenario” analysis approach. | 1. Sensitivity and specificity of IDx-DR using RV700 based on subject-level results against a Level I Prognostic Reference Standard (PRS)
2. Sensitivity and specificity of IDx-DR using RV700 based on eye-level results when compared to the Wisconsin Fundus Photograph Reading Center Level II Standard grading of the RV700 images
3. Sensitivity and specificity of IDx-DR using RV700 based on subject-level results when compared to the Wisconsin Fundus Photograph Reading Center Level II Standard grading of the RV700 images
4. Percent of total cases where a diagnostic result can be provided by IDx-DR with the RV700
5. Positive Predictive Value (PPV) and Negative Predictive Value (NPV) of IDx-DR with the RV700; repeat PPV and NPV calculations using the above weighted samples
6. Sensitivity and specificity of IDx-DR categorizing all PRS-determined positive cases with no diagnostic result as false negatives and all PRS-determined negative cases with no diagnostic result as false positives, i.e., a “worst case scenario” analysis of the impact of “Exam Quality Insufficient” results |

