**Supplementary Table 1: Eye-level diagnostic design parameters and pivotal study subject-level performance**

|             | Eye-level
Null Hypothesis
$p_0$ | Subject-level
Point Estimate
(two-sided 95% CI) |
|-------------|---------------------------------------|-------------------------------------------------------|
| Sensitivity | 75.0%                                 | 87.2% (81.8-91.2%)                                    |
| Specificity | 77.5%                                 | 90.7% (88.3-92.7%)                                    |

The primary efficacy analysis for the eye-level sensitivity analysis will be repeated for Level 1 using overweight sampling to achieve 20% mtmDR(+) with ETDRS level 53 or higher.

In addition, the primary analyses will be performed at the subject-level for regulatory submission and publication; this is consistent with the de novo study utilizing the Topcon NW400 retinal camera.

[figure not shown]

|                     |               |        |             |
|---------------------|---------------|--------|-------------|
| CTMF-SA-DXSDR006-03 | SAP_2.1_clean | Rev. A | Pg. 5 of 16 |
|---------------------|---------------|--------|-------------|

**2.2 Diagnostic Performance Study Secondary endpoints:** Secondary endpoints include estimation of test characteristics including positive predictive value (PPV), negative predictive value (NPV), and diagnosability. Other secondary endpoints include calculations of sensitivity and specificity that include each test's respective ungradable eyes in the denominator (see [Supplementary Table 2](#) below). One-sided 97.5% confidence intervals that account for inter-eye correlation will be presented as a measure of precision for all point estimates.

For secondary efficacy endpoints, the following will be analyzed:

- 1) Diagnosability: the percentage of total cases where a diagnostic result can be provided by IDx-DR with the RV700
- 2) Positive Predictive Value (PPV) and Negative Predictive Value (NPV) of IDx-DR with the RV700;
- 3) Sensitivity and specificity of IDx-DR as if all PRS-determined positive cases with no diagnostic result provided were false negatives and all PRS-determined negative cases with no diagnostic results were false positives, i.e., a "worst case scenario" analysis of the impact of "Exam Quality Insufficient" results

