### 2.3 Definitions for Primary and Secondary Endpoint Calculations

[Supplementary Table 2](#)

|               | Prognostic reference standard |           |            |           |
|---------------|-------------------------------|-----------|------------|-----------|
|               | Positive                      | Negative  | Ungradable | Total     |
| IDx-DR Result |                               |           |            |           |
| Positive      | PP                     | PN | PU  | DP |
| Negative      | NP                     | NN | NU  | DN |
| Ungradable    | UP                     | UN | UU  | DU |
| Total         | TP                     | TN | TU  | N  |

[figure not shown]

|                     |               |        |             |
|---------------------|---------------|--------|-------------|
| CTMF-SA-DXSDR006-03 | SAP_2.1_clean | Rev. A | Pg. 6 of 16 |
|---------------------|---------------|--------|-------------|

*Endpoints:*

$$\text{Sensitivity} = \frac{PP}{PP+NP}$$

$$\text{Specificity} = \frac{NN}{PN+NN}$$

$$\text{Positive Predictive Value} = \frac{PP}{PP+PN}$$

$$\text{Negative Predictive Value} = \frac{NN}{NP+NN}$$

$$\text{Diagnosibility} = \frac{PP+PN+NP+NN}{TP+TN}$$

*Endpoints considering ungradable eyes:*

$$\text{Sensitivity}_{+u} = \frac{PP}{PP+NP+UP}$$

$$\text{Specificity}_{+u} = \frac{NN}{PN+NN+UN}$$

$$\text{PPV}_{+u} = \frac{PP}{PP+PN+PU}$$

$$\text{NPV}_{+u} = \frac{NN}{NP+NN+NU}$$

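### One sentence in protocol 7.5 records the PRS as insufficient whenever IDx-DR fails, contradicting the rest of the plan; separately, the diagnosability formula does not match its stated denominator

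*Combined protocol and SAP*

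**What the plan says.** Protocol 7.5 describes what happens when six RV700 attempts (three before and three after dilation) give no result: "no further imaging attempts will be executed, PRS and the IDx-DR output for that/those eye(s) will be recorded as" 'Exam Quality Insufficient'. Read literally, this assigns the device's failure code to the reference standard as well.

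The same section then says "After the RV700 Imaging and AI Procedure is complete, subjects will advance to the PRS imaging protocol", with no exception for eyes that failed on the RV700. The images go to reading-centre experts "who will independently determine the prognostic reference standard (PRS) for each eye from the 4W & OCT images", and these experts "will be masked to each other and the IDx-DR diagnostic output". Whether the PRS is ungradable is the grader's decision: "If the image is insufficient in any way, the ophthalmologist can record a determination of" ungradable.

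SAP 2.2 words the endpoint as "Diagnosability: the percentage of total cases where a diagnostic result can be provided by IDx-DR with the RV700". The matching objective in SAP 2 is "the percentage of eyes for which a diagnostic result can be provided". The formula in SAP 2.3 and protocol 9.3.3 is (PP+PN+NP+NN)/(TP+TN). In the notation of that table the first letter is the IDx-DR result and the second is the PRS, so TP+TN counts only eyes with a PRS of positive or negative.

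**The concern.** The primary analysis uses only eyes gradable on both IDx-DR and the PRS (SAP 5.1, Missing Data). Diagnosability and the worst-case sensitivity and specificity are therefore the planned summary measures of what RV700 imaging failure costs. The camera is handheld and its operators have no previous fundus imaging experience, so failures are a natural question for this device.

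The 7.5 sentence, if used as the data-recording rule, would move every IDx-DR failure into the cell where both results are ungradable. The worst-case analysis would then have nothing to reclassify.

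The denominator is a separate matter and does not depend on that sentence. Eyes that are hard to image on both systems leave the diagnosability calculation altogether, although the endpoint wording includes them.

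**Working it through.** **Inputs.** The 3×3 table and formulas are in SAP 2.3 and protocol 9.3.3. The design values of 83.5% sensitivity and 87.1% specificity are in SAP Supplementary Table 4. The documents give no expected IDx-DR failure rate, PRS-ungradable rate or diagnosability. There is thus no stated figure to reproduce, and every rate below is an assumption.

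**1. The 7.5 sentence applied literally.** Every IDx-DR failure becomes PRS-ungradable, so UP = UN = 0. Then TP = PP+NP and TN = PN+NN, and

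- diagnosability = (PP+PN+NP+NN)/(PP+NP+PN+NN) = 100%;
- worst-case sensitivity = PP/(PP+NP+0) = primary sensitivity;
- worst-case specificity = NN/(PN+NN+0) = primary specificity.

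This holds at any failure rate. PPV and NPV with ungradable eyes use PU and NU instead, so they do not collapse in this way.

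**2. The PRS graded independently, as the rest of 7.5 requires.** Let f be the failure rate among PRS-gradable eyes, the same in both groups. Diagnosability is 1 − f, and each worst-case value is the primary value × (1 − f).

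| Assumed f | Diagnosability | Worst-case sensitivity | Worst-case specificity |
|---|---|---|---|
| 2% | 98% | 0.835×0.98 = 81.8% | 0.871×0.98 = 85.4% |
| 5% | 95% | 0.835×0.95 = 79.3% | 0.871×0.95 = 82.7% |
| 10% | 90% | 0.835×0.90 = 75.2% | 0.871×0.90 = 78.4% |
| 15% | 85% | 0.835×0.85 = 71.0% | 0.871×0.85 = 74.0% |

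Under the literal sentence every row would read 100%, 83.5% and 87.1%.

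In counts: take 200 truly PRS-positive eyes, 12 failures (6%) and 157 detections. Independent grading gives worst-case sensitivity 157/200 = 78.5%. The literal sentence gives 157/(200 − 12) = 157/188 = 83.5%, the same as the primary value.

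**3. The denominator alone, with the PRS graded independently.** Let u be the share of eyes that are PRS-ungradable and g the IDx-DR failure rate among them. The formula gives 1 − f. The all-eyes figure is (DP+DN)/N = (1 − u)(1 − f) + u(1 − g). The gap is u(g − f). With f = 6% the formula gives 94.0%, and:

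- u = 5%, g = 50%: 0.95×0.94 + 0.05×0.50 = 91.8%;
- u = 10%, g = 50%: 0.90×0.94 + 0.10×0.50 = 89.6%;
- g = 6%, either u: 94.0%, no gap.

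The formula therefore overstates diagnosability only if PRS-ungradable eyes fail IDx-DR more often than the others.

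**4. How the two interact.** Moving failures from UP and UN to UU changes neither DP+DN nor N. The all-eyes definition therefore gives the same diagnosability whichever way 7.5 is read. The worst-case analysis has no such protection.

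**The case against.** A reader might infer that the plan fixes diagnosability at 100% and makes imaging failures invisible. The documents do not support that. The inference rests on one sentence that the rest of the plan contradicts:

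- 7.5 itself requires masked grading of each eye from 4W and OCT images.
- SAP 2.1 and protocol 9.3.1 set the PRS by majority vote, with values positive, negative or ungradable. 'Exam Quality Insufficient' is a device output.
- The UP and UN cells, and the worst-case definition in SAP 2.2 and protocol 9.3.2, need eyes with a PRS but no IDx-DR result.
- SAP 5.1 lists reading-centre ungradable and IDx-DR ungradable as separate reasons for exclusion.
- The parallel substudy rule in protocol 7.6 records only the per-eye device output as insufficient.

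The words may well be a drafting slip. The SAP contains no such rule, and failures would still appear in the cross-tabulation and the flow diagram. All of this stands, and it makes the finding a contradiction to reconcile. It does not make the sentence harmless, because it sits in the operating procedure that says how results are recorded.

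On the denominator, the formula is explicit, identical in both documents, and uses the same PRS-determined eyes as the worst-case analysis. Aligning words and formula in either direction would remove the mismatch. That is fair. However, the objective and the endpoint both speak of eyes or total cases, so the formula is the part that departs from the stated aim.

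**Conclusion.** Two defects hold. First, the 7.5 sentence contradicts the rest of 7.5, the endpoint definitions, the exclusion categories and the substudy rule. If it were followed, diagnosability and the worst-case sensitivity and specificity would carry no information about RV700 failures. Second, the diagnosability formula does not measure the percentage of all eyes or cases that the plan states. This alone does not force 100%. It shifts the figure by u(g − f), which is 2.2 to 4.4 points in the half-failing illustration and zero if failure rates are equal.

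The algebra is certain. The sizes rest on assumed failure and ungradability rates. Primary sensitivity and specificity have the same formulas and values under either reading, because eyes without an IDx-DR result are excluded either way. Only secondary endpoints are affected, so the severity is moderate.

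**What to change.** In protocol 7.5, delete 'PRS and', so that only the IDx-DR output is recorded as insufficient and the PRS remains the reading-centre grade from the 4W and OCT images. In SAP 2.3 and protocol 9.3.3, define diagnosability as (DP+DN)/N to match the stated endpoint, and keep the TP+TN version as a labelled supplement.

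The cost is one sentence and one formula, the latter in two places. No new data are needed and the primary analysis does not change. Reported diagnosability may come out a few points lower than under the present formula.

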## 7.6 Precision Substudy IDx-DR Exam Procedure

Select subjects will be invited back for the Precision Substudy based on the PRS grading of their Diagnostic Performance Study images. Eighteen (18) of the Precision Substudy subjects will have received a grade of mtmDR(+) in at least one eye, and eighteen (18) will have received a grade of mtmDR(-) in both eyes. These subjects will undergo the IDx-DR Exam Procedure as outlined in Section 1.3.1-1.3.4. First, Tropicamide 1% eye drops will be administered by qualified site staff under medical supervision. The subject will then be asked to wait at least 30 minutes or until the pupils are dilated to at least 5 mm. The fully dilated subject will then undergo nine IDx-DR exams. The substudy will test three RV700 cameras, and three camera operators with three pre-specified replicates, such that each subject will complete nine pairs of imaging exams. The camera, operator and replicate combinations across subjects are outlined below:

|         |                                     |
|---------|-------------------------------------|
| Exam A: | RV700 A + Operator #1 (Replicate 1) |
| Exam B: | RV700 A + Operator #2 (Replicate 1) |
| Exam C: | RV700 A + Operator #2 (Replicate 2) |
| Exam D: | RV700 B + Operator #2 (Replicate 1) |
| Exam E: | RV700 B + Operator #3 (Replicate 1) |
| Exam F: | RV700 B + Operator #3 (Replicate 2) |

---

**Digital Diagnostics Confidential.** This document is intended for internal use only and may not be disclosed or reproduced in whole, or in part, for external distribution in any form without express written permission of DDx Legal. All hard copies should be checked against the current electronic revision prior to use and destroyed promptly thereafter. All hard copies are considered uncontrolled documents.

Exam G: RV700 C + Operator #1 (Replicate 1)  
Exam H: RV700 C + Operator #1 (Replicate 2)  
Exam I: RV700 C + Operator #3 (Replicate 1)

Operators will be instructed to reposition subjects between each imaging replicate. Operators will also be instructed to give subjects at least five minutes between exams to have time for adequate pupil recovery. If within a given exam the subject is unable to receive a diagnostic result in one or both eyes, the procedure will be repeated. If after three attempts a diagnostic result is not received and the subject has not already been re-dilated, Tropicamide 1% eye drops will be re-administered by qualified site staff under medical supervision. If after another three attempts a diagnostic result is not received, the per-eye output will be recorded as “Exam Quality Insufficient”, and the subject will continue to the next IDx-DR Exam until all nine exams are completed. In no circumstance will a subject receive Tropicamide more than twice in the substudy. This workflow is shown visually in Section 1.3.3.

The camera operators for this procedure will be operators with no previous retinal imaging experience. The Sponsor will ensure the site has three operators who are able to complete an IDx-DR training program on the RV700. Operators will be masked from all IDx-DR results and any diagnostic information used to select the subject for the substudy, except in the case where no diagnostic result can be provided, and the device output is “Exam Quality Insufficient”. In that case, the operator will be notified to attempt the exam again, re-dilate after three failed attempts, or after an additional three failed attempts, consider the device output for that eye in that exam to be “Exam Quality Insufficient”, and proceed with the next exam.

The Precision Substudy IDx-DR Exam Procedure may take more than three hours to complete. If the subject’s pupils constrict to less than 5mm, Tropicamide 1% eye drops will be re-administered by qualified site staff under medical supervision.

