| Planned # of Sites | At least 2 primary care sites                                                                                                                                                                                                                                                                                                                                                                                                                                                                                                                                             |
| Subject Population | Adults, 22 years or older, living with diabetes, that have not been previously diagnosed with retinal disease.                                                                                                                                                                                                                                                                                                                                                                                                                                                            |
| Sample Size        | A minimum of 200 eyes with mtmDR and 140 eyes without mtmDR will be enrolled in the main diagnostic performance study, and, of those subjects, 36 will also be enrolled in the precision substudy.                                                                                                                                                                                                                                                                                                                                                                        |
| Subject Duration   | 
Participation in the main study, the diagnostic performance study, will require two to three hours per subject to complete the RV700 imaging and the imaging required by the retinal reading center.
 
Participation in the precision substudy will require approximately five hours per subject to complete the set of nine RV700 imaging procedures.
                                                                                                                                                                                                        |

---

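### Protocol 7.6 limits substudy subjects to two Tropicamide administrations, but its constriction rule can call for a third, and no order of precedence is given

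*Combined protocol and SAP*

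**What the plan says.** All of the dosing statements are in Protocol 7.6.

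- **Start of session.** Each substudy subject is dilated before imaging: "First, Tropicamide 1% eye drops will be administered by qualified site staff under medical supervision".
- **Failed attempts, main text.** After three attempts without a result, the drops are repeated subject to a condition: "and the subject has not already been re-dilated, Tropicamide 1% eye drops will be re-administered".
- **Limit.** "In no circumstance will a subject receive Tropicamide more than twice in the substudy".
- **Failed attempts, operator paragraph.** Operators are told to "re-dilate after three failed attempts". The condition is not repeated here.
- **Constriction, last paragraph.** If "pupils constrict to less than 5mm, Tropicamide 1% eye drops will be re-administered by qualified site staff under medical supervision". This sentence has no condition on earlier re-dilation and does not mention the limit.

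On session length, 7.6 says "The Precision Substudy IDx-DR Exam Procedure may take more than three hours to complete", and the Synopsis (1.1, Subject Duration) says participation "will require approximately five hours per subject to complete the set of nine RV700 imaging procedures".

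For the workflow, 7.6 sends the reader to Section 1.3.3. In the body of the protocol, 1.3.3 is the table of camera and operator configurations, and the exam procedure figure is under 1.3.2. The table of contents still lists the exam procedure as 1.3.3.

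**The concern.** One sentence sets an absolute limit on how often a research subject receives a drug. Another sentence in the same section directs staff to give the drug again on a clinical sign, without tying that direction to the limit. A site whose subject has had two administrations and whose pupils then fall below 5 mm finds one sentence telling it to act and another telling it not to. Protocol 8.2.10 defines a deviation as an event not in accordance with the protocol's requirements, so on the bare text either action could be recorded as one.

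Subject protection comes first, because a stated exposure limit should not be open to doubt. Uniform conduct of the substudy comes second. Dilation and sequence are terms in the precision mixed model (SAP 5.2; Protocol 8.1), and average ungradable agreement is an endpoint, so the pupil condition under which later exams are taken matters to what is being measured. The substudy has 36 subjects, and Protocol 4.1 provides for the three-camera, three-operator set-up at two sites. It therefore matters that both sites work from the same instruction.

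**Working it through.** The protocol's stated figure is a maximum of 2 administrations per subject. There is no power or precision calculation to reproduce. The check is to count administrations under the protocol's own rules and compare the count with 2.

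**Inputs, all from Protocol 7.6**
- Initial dilation: 1 for every subject.
- Failed-attempt rule in the main text: adds 1, only if the subject has not already been re-dilated.
- Failed-attempt instruction in the operator paragraph: adds 1, with no such condition stated.
- Constriction rule: adds 1 when pupils fall below 5 mm, with no such condition stated.

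**Formula:** total = 1 (initial) + re-dilations for failed attempts + re-dilations for constriction.

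| Course of the session | Total ordered | Against the limit of 2 |
|---|---|---|
| No re-dilation | 1 | within |
| One failed-attempt re-dilation | 1 + 1 = 2 | at the limit |
| One constriction re-dilation | 1 + 1 = 2 | at the limit |
| Failed-attempt re-dilation, then pupils below 5 mm | 1 + 1 + 1 = 3 | above |
| Pupils below 5 mm, re-dilated, then below 5 mm again | 1 + 2 = 3 | above, if the rule applies a second time |
| One re-dilation, then three failed attempts, main text | 2 (condition blocks a third) | at the limit |
| One re-dilation, then three failed attempts, operator paragraph as worded | 1 + 1 + 1 = 3 | above |

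Three things follow.

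1. Through the first re-dilation, from either trigger, all the sentences can be followed together.
2. The main failed-attempt rule never breaches the limit, because its own condition stops it at 2. The constriction sentence has no such stop. This contrast within one section is what creates the doubt.
3. The operator paragraph, taken literally, has no stop either. One re-dilation in each of nine exams would give 1 + 9 = 10. That is an arithmetic ceiling on the loosest wording, not a forecast. The paragraph is more naturally read as a shortened restatement of the conditional rule.

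The frequency of the conflict cannot be computed. It would need the rate at which dilated pupils fall below 5 mm during a session, and the rate of failed attempts. The documents give neither, nor a duration of effect for the drops.

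**The case against.** The best reply is that the limit is worded universally and covers the whole substudy, so it governs every re-administration in the section. On that reading there are two triggers for a repeat and a ceiling of two on the total, and nothing conflicts. The constriction sentence is an ordinary conditional and does not say that it applies each time. This reading is plausible. But the text does not state precedence, and the section writes a condition into one trigger and omits it from the other. Even if the limit governs, 7.6 does not say what is done with a subject who has reached it and whose pupils then fall below 5 mm.

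A reader might infer more than the documents support:

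- **That sites can never follow both rules.** They can, through one re-dilation. The conflict is conditional.
- **That the protocol orders unlimited repeats.** The constriction sentence is silent on a limit. It does not order repeats without one.
- **That a third administration is likely because sessions last three to five hours.** No figure in the documents links elapsed time to pupils below 5 mm. The remark in Protocol 4.2 that repeated imaging constricts pupils explains why undilated subjects would need recovery time, and dilating everyone is the stated response. The presence of a constriction rule in 7.6 shows only that the event was foreseen.
- **That some sites will exceed the limit while others image constricted pupils.** This is a prediction of behaviour. Administration is under medical supervision, and eyes that yield no result already have a defined output.
- **That administrations go unrecorded.** The case report form is not among the documents, and dilation is already a model covariate.

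The workflow figure might settle the point. It is not shown in the copy available, so no claim is made about whether it agrees with the text.

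**Conclusion.** The inconsistency is real but narrow. It is confined to Protocol 7.6 and arises once a subject has had two administrations and either the pupils fall below 5 mm again or, on the operator paragraph's wording, three further attempts fail. At that point the text calls for a third administration that the stated limit of two forbids, and it names no rule that prevails.

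The size is one administration above the limit at the first conflict, in an unknown number of at most 36 subjects. Any effect on the dilation and sequence terms or on ungradable agreement is possible but unquantified. The co-primary sensitivity and specificity results come from the Diagnostic Performance Study and are not affected.

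The conclusion rests on the text alone and assumes that the unseen workflow figure does not resolve the matter. The point is worth correcting because it concerns drug exposure in research subjects and the correction is simple. Nothing here says which of the two rules is right.

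**What to change.** The sponsor and investigators should reconcile the limit, the constriction sentence and the two failed-attempt statements in Protocol 7.6 into one consistent instruction. It should state how the limit and the triggers relate, and what applies to a subject who has already reached the stated limit. The content of that instruction is a clinical matter for them.

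In the same revision, the workflow reference in 7.6 should be corrected, since it cites Section 1.3.3 while the exam procedure stands under 1.3.2. The figure should be checked against the reconciled text.

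The cost is a protocol clarification and a notice to the substudy sites, with IRB approval under Protocol Section 10 if it is issued as an amendment. Sample size, endpoints and analysis methods do not change.
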